## Protocol Title: Evaluating Trikafta for the treatment of patients with non-cystic fibrosis bronchiectasis (NCFBE)

Trikafta™ is not prescribed or approved for NCFBE and has not been considered of benefit for patients with NCFBE. We hypothesize that a drug such as Trikafta™, that markedly activates both wild type and mutant CFTR *in vivo*, will enhance mucociliary clearance and should improve respiratory function (FEV1) in a subset of patients with NCFBE. Even if one in ten patients with NCFBE shows significant improvement in FEV1 following Trikafta™, this would constitute a major discovery and provide new hope for tens of thousands of individuals in the US with an otherwise untreatable and lethal lung disease.

Figure 1. Summary of trial design.

[figure not shown]

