**Sample size**

We will test the null hypothesis that the true Trikafta™ response rate of NCFBE individuals is  $\leq 1\%$  vs. the alternative hypothesis that the true Trikafta™ response rate is  $\geq 15\%$ . We will initially enroll 16 subjects. If none of these subjects exhibit a clinical response (defined as  $> 5\%$  improvement of % predicted FEV1 from baseline), the study may be considered for termination. Otherwise, we intend to enroll a total sample size of 29 individuals (or 30 subjects, in the unlikely event that an individual discontinues participation; i.e., subjects who do not complete the study will be replaced). In this design, if Trikafta™ is ineffective, the probability of early termination after 16 subjects is 85% and only a 2.8% chance of concluding the drug is effective (type I error). If Trikafta™ is effective, there is a 90.04% chance of reaching this conclusion. If fewer than 2 patients (of 29 patients total) of the overall cohort show a clinical effect, Trikafta™ will be considered ineffective. To demonstrate the ability of iPS cells to predict clinical benefit, 16 (29) patients will provide at least 80% power to detect a significant Spearman correlation of at least  $r = 0.8$  (.53) between the changes in clinical outcomes with changes in short circuit current as measured in iPS cells. Tabular details of this analysis are provided below. Power calculations were performed using PASS v. 14 (Kaysville, UT) with a two-sided Z-test and a significance level of 0.05.

|                            | Cumulative # of responses | Decision                                                                                                             | 95% Confidence Interval (CI) |
|----------------------------|---------------------------|----------------------------------------------------------------------------------------------------------------------|------------------------------|
| Stage 1: Enter 16 subjects | 0                         | Consider Termination of the trial because the agent is ineffective.
Response rate is <math>\leq 1\%</math> | LB of 95% CI is $< 1\%$      |
|                            | At least 1                | Inconclusive result, continue                                                                                        | 95% CI contains 1%           |

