**Protocol Title: Evaluating Trikafta for the treatment of patients with non-cystic fibrosis bronchiectasis (NCFBE)**

|                                                                                                                                                                                                                                   |                                   |                                                                                      |                                       |
|-----------------------------------------------------------------------------------------------------------------------------------------------------------------------------------------------------------------------------------|-----------------------------------|--------------------------------------------------------------------------------------|---------------------------------------|
|                                                                                                                                                                                                                                   |                                   | trial (proceed to stage 2).                                                          |                                       |
| Stage 2: Enter 14 additional subjects                                                                                                                                                                                      | 1 or less
(stage I + stage II) | Consider that the agent is ineffective. Response rate is $\leq 1\%$                  | LB of 95% CI is less than 1%          |
|                                                                                                                                                                                                                                   | 2 or more
(stage I + stage II) | Drug may be effective
Response rate is greater than 1% and not different from 15% | 95% CI contains 15% and LB is $> 1\%$ |
|                                                                                                                                                                                                                                   | 6 or more
(stage I + stage II) | Drug is effective
Response rate is at least 15%                                   | 95% CI LB $\geq 15\%$                 |

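### The decision table turns failure to show a response rate above 1% into a finding that the rate is at most 1%, which no count in a trial of 29 or 30 subjects can support

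*Protocol*

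**What the plan says.** The protocol, Section 7 (Sample size), sets up a two-stage test: "We will test the null hypothesis that the true Trikafta™ response rate of NCFBE individuals is" at most 1%, "vs. the alternative hypothesis that the true Trikafta™ response rate is" at least 15%. On numbers it says "We will initially enroll 16 subjects". With no responder among the 16, termination may be considered. Otherwise enrolment continues to 29, or 30 to cover a dropout. The final rule in the text is: "If fewer than 2 patients (of 29 patients total) of the overall cohort show a clinical effect, Trikafta™ will be considered ineffective".

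The decision table attaches conclusions to the counts:

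- Stage 1, 0 responders: "Consider Termination of the trial because the agent is ineffective", with a response rate of at most 1%. The interval column gives a lower bound below 1%.
- Stage 1, 1 or more: inconclusive, continue. The interval column says that the interval contains 1%.
- Stage 2, 1 or fewer in total: "Consider that the agent is ineffective. Response rate is" at most 1%. The interval column reads "LB of 95% CI is less than 1" percent.

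The table's note defines an abbreviation for the upper bound, but no row uses it. Earlier in Section 7 the protocol requires an exact 95% interval for the response rate by Blaker's method.

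**The concern.** A lower bound below 1% means that the data do not rule out rates of 1% or less. It does not mean that they rule out rates above 1%. The two negative rows read non-rejection of the null as proof of it.

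The table is also uneven with itself. It calls a Stage 1 result inconclusive on the ground that the interval contains 1%. The intervals for 0/16 and 1/29 contain 1% too, yet those rows carry a definite conclusion. At 1/29 the observed rate, 1/29 = 3.4%, is itself above the ceiling that the table states.

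At stake is what a negative trial would be said to have shown. The Background section argues that a modest response rate would matter: "Even if one in ten patients with NCFBE shows significant improvement" in FEV1, the protocol would regard that as a major discovery. A conclusion of at most 1%, drawn from data compatible with 10% or 15%, could be quoted as settling a question that the trial left open.

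**Working it through.** **Inputs** (protocol, Section 7): null rate 1%, target rate 15%, Stage 1 n = 16 with a possible stop at 0, total n = 29 (30 in the table, as 16 + 14), negative conclusion at 1 or fewer, Blaker 95% interval.

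**1. The plan's own figures.** With the stop at 0/16 applied, a negative result is either 0 of 16, or exactly 1 of 16 followed by 0 of 13:

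P(negative | p) = (1−p)^16 + 16p(1−p)^15 × (1−p)^13 = (1−p)^16 + 16p(1−p)^28

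- Early stop at 1%: 0.99^16 = 0.851 (stated 85%).
- Type I error: 1 − (0.8515 + 0.16 × 0.7547) = 0.0278 (stated 2.8%).
- Power at 15%: 1 − (0.0743 + 2.4 × 0.01056) = 0.9004 (stated 90.04%).

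All three reproduce.

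**2. Intervals for the counts that carry the label.** Blaker's method keeps a rate p if a + b ≥ 0.05. Here a is the smaller of P(X ≤ x | p) and P(X ≥ x | p), and b is the largest probability in the opposite tail that does not exceed a. Clopper-Pearson is shown for comparison. The last column is the chance of so few responders if the true rate is 15%.

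| Count | Blaker 95% | Clopper-Pearson 95% | Includes 15%? | P(count or fewer, given 15%) |
|---|---|---|---|---|
| 0/16 | 0–20.1% | 0–20.6% | yes | 7.4% |
| 1/29 | 0.18–16.6% | 0.09–17.8% | yes | 5.5% |
| 1/30 | 0.17–16.3% | 0.08–17.2% | yes | 4.8% |
| 0/29 | 0–11.0% | 0–11.9% | no | 0.9% |
| 0/30 | 0–10.6% | 0–11.6% | no | 0.8% |

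No upper bound comes near 1%. Even with zero responders, a Clopper-Pearson upper bound of 1% needs 0.99^n ≤ 0.025, so n ≥ ln 0.025 / ln 0.99 = 367.04, or 368 subjects.

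**3. How often the label would be attached.** With the stop always applied, the formula in step 1 holds. With the stop never applied and n = 29, P(1 or fewer of 29) = (1−p)^29 + 29p(1−p)^28.

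| True rate | Stop never applied | Stop always applied |
|---|---|---|
| 5% | 0.226 + 0.345 = 57.1% | 0.440 + 0.190 = 63.0% |
| 7.5% | 34.9% | 42.3% |
| 10% | 0.047 + 0.152 = 19.9% | 0.185 + 0.084 = 26.9% |
| 15% | 0.009 + 0.046 = 5.5% | 0.074 + 0.025 = 10.0% |

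At each of these rates, a statement that the rate is at most 1% would be false.

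**The case against.** Calling a drug ineffective is common shorthand for a no-go in a two-stage design, and part of the wording is hedged as something to consider. The decision follows the count, not the interval, and its error rates are disclosed and right. The roughly 10% chance of a wrong negative at 15% is simply one minus the stated power. Rates between 1% and 15% carry no promised error rate. The plan already requires an exact interval with the response rate, so a reader would see the wide range. Section 20 describes the trial as preliminary and not meant for regulatory submission.

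Most of this stands, and it limits the harm. It does not rescue the numerical statement. The table does more than say no-go: it gives a ceiling of 1% for the rate and sets only a lower bound beside it. Reporting the interval elsewhere would put two incompatible statements in the same report.

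Two stronger readings are tempting, and the protocol supports neither:

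- A reader might infer that every count with this label leaves 15% open. That would be so only if 0/16 always ended the trial. The protocol makes the stop optional, so 0/29 or 0/30 can occur, and these exclude 15%.
- A reader might infer that any lower bound below 1% leads to the label. It does not: 1/16 has a Blaker lower bound of 0.32% and is labelled inconclusive.

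**Conclusion.** The point holds as a fault of stated inference, not of design. For 0/16, and for 1 or fewer responders at Stage 2, the conclusion that the response rate is at most 1% does not follow. At 0/16, 1/29 and 1/30 the data remain compatible with the 15% target. At 0/29 and 0/30 they exclude 15% but still allow rates up to about 11%. The unsupported label would be attached in 57–63% of trials at a true rate of 5%, 20–27% at 10% and 5.5–10% at 15%.

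These figures rest on n = 29 for the probabilities and on fixed-sample intervals not adjusted for the two stages. Reading the Background's one-in-ten rate as 10% in the enrolled subset is an assumption, since that passage speaks of all patients with the disease. The boundaries, the sample size and the stated 85%, 2.8% and 90.04% need no change.

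**What to change.** In both negative rows of the decision table, replace the statement of a rate of at most 1% with *response rate not shown to exceed 1%*. Replace the lower-bound entry with the full exact 95% interval for the observed count and the actual n, noting that it is a fixed-sample interval not adjusted for two stages. Giving the interval by observed count also covers 0 and 1 responders, and 29 and 30 subjects, in the same row. Allow *response rate below 15%* only if the upper bound is below 15%. In the sample size paragraph, replace the verdict of ineffective with *considered not shown to be effective*.

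The cost is one sentence and two table rows. Data, sample size and decision counts are untouched. The downside is that a negative conclusion becomes less definite.

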**Protocol Title: Evaluating Trikafta for the treatment of patients with non-cystic fibrosis bronchiectasis (NCFBE)**

|                                                                                                                                                                                                                                   |                                   |                                                                                      |                                       |
|-----------------------------------------------------------------------------------------------------------------------------------------------------------------------------------------------------------------------------------|-----------------------------------|--------------------------------------------------------------------------------------|---------------------------------------|
|                                                                                                                                                                                                                                   |                                   | trial (proceed to stage 2).                                                          |                                       |
| Stage 2: Enter 14 additional subjects                                                                                                                                                                                      | 1 or less
(stage I + stage II) | Consider that the agent is ineffective. Response rate is $\leq 1\%$                  | LB of 95% CI is less than 1%          |
|                                                                                                                                                                                                                                   | 2 or more
(stage I + stage II) | Drug may be effective
Response rate is greater than 1% and not different from 15% | 95% CI contains 15% and LB is $> 1\%$ |
|                                                                                                                                                                                                                                   | 6 or more
(stage I + stage II) | Drug is effective
Response rate is at least 15%                                   | 95% CI LB $\geq 15\%$                 |
| LB = Lower Bound, UB = Upper Bound
Note: Thirty total patients will be enrolled in the unlikely event that a subject discontinues participation (e.g., due to elevated liver function tests, skin rash, or for other reasons). |                                   |                                                                                      |                                       |

With a sample size of 16 (29) participants, we anticipate a 97% (>99%) power to detect a mean sweat chloride decrease of 10 mmol/L assuming a standard deviation of 9.7 mmol/L (Boyle, Bell et al. 2014, Vermeulen, Le Camus et al. 2017) under a two-sided 0.05 alpha-level paired t-test. With a higher standard deviation of 15 mmol/L, the power decreases to 70.3% (93.4%) to detect a mean decrease of 10, but we retain 96.2% (>99%) power to detect the hypothesized mean decrease of 15 mmol/L with a sample size of 16 (29) patients.

SAEs and AEs will be tabulated using standard coding terms sorted by System Organ Class (SOC). The incidence of AEs will be tabulated by seriousness and severity. The number of SAEs and AEs will be summarized as follows: (i) The proportion of subjects with at least one (S)AE, (ii) The average number of (S)AEs per subject, and (iii) The rate of (S)AEs per subject week of follow-up.

**Expected Outcomes** Subjects will be recruited by study investigators as above. Please note that based on considerable past experience conducting clinical trials and past collaborations with NCFBE clinical leadership throughout the US, we do not have concerns regarding our ability to perform the patient-oriented study described here, or to propagate and characterize iPS cells (Crane, Kramer et al. 2015, Mou, Brazauskas et al. 2015, Hawkins, Kramer et al. 2017, Jacob, Morley et al. 2017). The ‘main’ study protocol will evaluate the clinical benefit of Trikafta™ in patients with NCFBE. In addition, the study will furnish one test of our hypothesis that thresholds of CFTR activity in differentiated iPS cells *in vitro* predict benefit following Trikafta™ *in vivo*. If a strong correlation can be established between Trikafta™ response *in vitro* and *in vivo* (e.g., FEV1), the clinical results will provide evidence regarding usefulness of *in vitro* models for predicting clinical efficacy in this setting.

**Scientific Rigor** All *in vitro* and *in vivo* studies will be conducted with appropriate “n” so that therapeutically relevant conclusions can be drawn. Multiple biologic or technical replicates will be performed and evaluated in blinded fashion by an experienced statistician. NCFBE is represented in both sexes, and we expect equal enrollment of male and female individuals.

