### **7. Statistical Analysis Plan**

Goals of the 'main' study are to determine the clinical response to Trikafta™ and whether *in vitro* responsiveness of iPS cell-derived airway monolayers predict Trikafta™ effectiveness. Primary outcomes comprise the ability of iPSC-derived monolayers to predict respiratory benefit from Trikafta™ after 4 weeks of *in vivo* treatment. Primary analysis will include an estimate of clinical response rate of Trikafta™ at week 4 of treatment and a 95% confidence interval using the exact method proposed by Blaker (Blaker, 2000). A responder is defined as any subject with an improvement, from baseline, in  $FEV_1 > 5\%$  predicted.  $FEV_1$  will also be considered continuously. A two-sided 0.05 alpha level paired t-test comparing the baseline and week 4  $FEV_1$  measurements, along with the test and 95% associated confidence interval, will be evaluated.

In this study, if at least 15% of subjects meet the definition of responder, we will view this as initial evidence of a favorable result. Overall response rate will be accompanied by an exact 95% confidence interval. To determine the role of iPS *in-vitro* response to Trikafta™, we will compare the  $\Delta$  Isc (change in Isc) among Trikafta™ responders and Trikafta™ non-responders using an ANCOVA test. Additionally, we will correlate the  $\Delta$  Isc obtained from *in vitro* experiments with the change in FEV1% predicted (post minus pre) using Spearman's rank-order correlation with an associated 95% confidence interval. We will also test whether the iPS response reaches a CFTR functional threshold of 30% wild-type levels (a magnitude of activity in primary airway epithelial cells viewed as potentially relevant to clinical benefit). In a sensitivity analysis, we will replicate the FEV1 analysis with sweat chloride responses and determine the *in vivo* response rate.

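### The Stage 2 row for 2 or more responders declares the rate no different from 15% only because the 95% interval contains 15%, which it does at every count where that row is the final conclusion

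*Protocol*

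**What the plan says.** Section 7 (Sample size) sets a null response rate of at most 1% against the alternative that "the true Trikafta™ response rate is" at least 15%. The trial has two stages: "We will initially enroll 16 subjects. If none of these subjects exhibit a clinical response", termination may be considered; otherwise "we intend to enroll a total sample size of 29 individuals", or 30 to allow for a discontinuation. The closing rule is: "If fewer than 2 patients (of 29 patients total) of the overall cohort show a clinical effect, Trikafta™ will be considered ineffective".

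The decision table then attaches conclusions to counts. For 2 or more responders over both stages it says that the drug may be effective and adds "Response rate is greater than 1% and not different from 15" per cent. The column beside it gives the basis: "95% CI contains 15% and LB is" above 1%. A separate row for 6 or more responders calls the drug effective with a rate of at least 15%.

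Earlier in Section 7, the response rate is to be reported with Blaker's exact 95% interval, and a bar is set on the observed proportion: "if at least 15% of subjects meet the definition of responder, we will view this as initial evidence of a favorable result".

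**The concern.** An interval that contains 15% shows only that the data have not excluded 15%. Turning that into a conclusion of no difference needs a margin, and an interval narrow enough to lie inside it. The table has no margin, and with 29 subjects the interval is wide.

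The design tests 1% against 15%. Rejecting 1% supports the first half of the cell, that the rate exceeds 1%. It does not support the second half. Section 20 says the results are meant to help guide more extensive studies of this drug in this disease. Someone planning such a study could take a fixed protocol conclusion of no difference from 15% as support for 15% as a planning value, when the observed rate was less than half of that.

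**Working it through.** **Inputs.** Null 1%, target 15%, stage 1 of 16 subjects with a possible stop at 0, total 29, success at 2 or more (Section 7, Sample size). Interval: Blaker exact, 95% (Section 7, primary analysis).

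**Step 1: reproduce the plan's own figures.** With q = 1 − p and 13 further subjects in stage 2, success fails only if stage 1 has no responder, or has exactly one and stage 2 has none:

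P(success) = 1 − q^16 − (16·p·q^15)·q^13 = 1 − q^16 − 16·p·q^28

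- p = 1%: 0.99^16 = 0.8515 (stated early termination 85%). P(success) = 1 − 0.8515 − 0.1208 = 0.028 (stated 2.8%).
- p = 15%: P(success) = 1 − 0.0743 − 0.0253 = 0.9004 (stated 90.04%).

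The design figures are correct.

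**Step 2: intervals by count.** For count x, let γ(p; x) be the smaller of P(X ≥ x) and P(X ≤ x) under Binomial(29, p). The Blaker interval holds every p for which P[γ(p; X) ≤ γ(p; x)] exceeds 0.05.

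| Responders of 29 | Observed | Blaker 95% interval | Contains 15% and lower bound above 1%? |
|---|---|---|---|
| 1 | 3.4% | 0.18% to 16.6% | No (lower bound) |
| 2 | 6.9% | 1.24% to 21.6% | Yes |
| 3 | 10.3% | 2.9% to 26.9% | Yes |
| 4 | 13.8% | 4.9% to 30.5% | Yes |
| 5 | 17.2% | 7.1% to 35.7% | Yes |
| 6 | 20.7% | 9.4% to 39.3% | Yes |
| 7 | 24.1% | 11.0% to 42.9% | Yes |
| 8 | 27.6% | 13.6% to 46.5% | Yes |
| 9 | 31.0% | 16.4% to 50.0% | No (15% excluded) |

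The table's own stage sizes, 16 + 14, add to 30. With 30 subjects the same counts qualify: 2/30 gives 1.2% to 20.9%, 8/30 gives 13.1% to 44.9%, and 9/30 has a lower bound of 15.8%.

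From 6 responders upward the next row also applies, so the row at issue is the highest one reached only at 2 to 5. At all four of those counts the interval contains 15%.

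**Step 3: compare with the protocol's own bar.** 15% of 29 is 4.35, so at least 5 responders are needed to meet it. Counts of 2, 3 and 4 fall short, yet each receives the statement of no difference from 15%. At 2 of 29 the observed rate is 6.9/15 = 46% of the target.

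**Step 4: how often the row is the final conclusion.** P(2 to 5) = P(2 or more) − P(6 or more) under the two-stage rule:

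| True rate | P(2 or more) | P(6 or more) | P(2 to 5) |
|---|---|---|---|
| 5% | 0.370 | 0.003 | 0.367 |
| 7.5% | 0.577 | 0.019 | 0.559 |
| 10% | 0.731 | 0.064 | 0.667 |
| 15% | 0.900 | 0.261 | 0.639 |

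The row is reached almost as often at half the target rate as at the target itself: 0.559/0.639 = 0.87.

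**The case against.** The cell is hedged. It says only that the drug may be effective, and the adjacent column states the literal basis, so the disputed words can be read as shorthand for an interval that does not exclude 15%. The table keeps a separate row for a rate of at least 15%. Section 7 already requires the rate with its exact interval, so 2 of 29 would appear as 6.9% (1.2% to 21.6%). The bar for a favorable result is on the observed proportion, and nothing says the table overrides it. The go/no-go rule and the error rates are untouched, and a test of 1% against 15% was never meant to separate 5% from 15%. The study is small and open-label, and Section 20 says its data will not go to the FDA.

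Most of this stands and limits the weight of the point. It does not rescue the phrase. The hedge concerns efficacy, while the statement about the rate beside it is unqualified. Because the design cannot separate 5% from 15%, the table should not draw a conclusion about 15% from a wide interval.

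A reader might infer three stronger things that the documents do not support:

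- *That the drug is declared equal to target.* The cell does not say so, and reaching the target has its own row.
- *That no result could show a rate below 15%.* The stop at 0 of 16 is only to be considered. If the trial continued to 0 of 29, the upper bound would be 11.0% (10.6% for 0 of 30), which excludes 15%.
- *That a drug at half the target is always mislabelled.* Given 2 to 5 responders the interval contains 15% by construction, so a miss rate computed on that condition is circular. The unconditional chance at 7.5% is 56%.

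**Conclusion.** The conclusion of no difference from 15% is unsupported as written. At the counts where this row is the highest one reached (2 to 5), the interval condition always holds, so the phrase tells the reader nothing about 15% beyond the count itself. It would be attached to 2, 3 and 4 of 29, which miss the protocol's own 15% bar, with probability of finishing in the row of 37%, 56% and 64% at true rates of 5%, 7.5% and 15%. The other half of the cell, that the rate exceeds 1%, is supported.

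This is a fault in a prespecified conclusion, not in the design. It rests on two assumptions. First, the table uses the Blaker interval named for the primary analysis, computed as for a single sample of 29. With Clopper-Pearson, 15% is still contained from 2 to 8 of 29, but at 2 of 29 the lower bound is 0.85%, so that count would fail the row's 1% condition. Second, the probabilities assume the trial stops when stage 1 has no responder. The row for 6 or more responders raises a separate question that this point does not rely on.

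**What to change.** In the Stage 2 row for 2 or more responders, keep the statement that the drug may be effective and replace the rate statement with: *Response rate is greater than 1%; a rate of 15% is neither established nor excluded.* Draw a conclusion about 15% only when the interval excludes it on one side. No new reporting rule is needed, because Section 7 already calls for the response rate with its exact 95% interval.

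The cost is one table cell and a slightly less favorable stated conclusion. Sample size, decision counts, type I error and power stay as they are.

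### The decision table's top tier does not meet its own criterion: 6 responders of 29 give a lower 95% bound of about 9%, and 15% is first reached at 9 responders

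*Protocol*

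**What the plan says.** Section 7 (Statistical Analysis Plan) makes the week 4 response rate a primary analysis, with a "95% confidence interval using the exact method proposed by Blaker". The Sample size subsection tests a true response rate of at most 1% against one of at least 15%. On size it says "We will initially enroll 16 subjects" and then "we intend to enroll a total sample size of 29 individuals", or 30 to allow for a dropout. The table's Stage 2 heading is "Enter 14 additional subjects", which makes 30.

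The decision table ties responder counts to a conclusion and to a property of the 95% interval:

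- Stage 1, no responders in 16: consider termination; rate at most 1%; lower bound below 1%.
- Stage 1, one or more: continue; "95% CI contains 1" percent.
- Stage 2, one or fewer in total: consider the drug ineffective; rate at most 1%; lower bound below 1%.
- Stage 2, two or more: may be effective; interval contains 15%, lower bound above 1%.
- Stage 2, six or more: drug is effective; "Response rate is at least 15" percent; lower bound at or above 15%.

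**The concern.** The last row states a count, a conclusion and an interval criterion, and the count does not satisfy the criterion. Six of 29 is 20.7%. At this sample size a two-sided 95% interval around that estimate extends well below 15%. With 6, 7 or 8 responders the interval column would place the result in the row that does not distinguish the rate from 15%, while the count column would place it in the row that declares the drug effective. The same data would get two verdicts, and the count would support the trial's strongest claim without evidence for it.

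Two other parts of the table overreach in the same way. The stage 1 row on one or more responders describes an interval that is correct for only one count. The two negative rows turn a failure to exclude 1% into a conclusion that the rate is at most 1%.

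**Working it through.** **Inputs (Protocol Section 7).** Stage 1 size 16; total 29 (30 by the table); null rate 1%; alternative 15%; ineffective if fewer than 2 responders of 29; two-sided 95% Blaker interval.

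**Step 1. Reproduce the stated design figures (n = 29).**
- Early termination at 1%: 0.99^16 = 0.851 (stated 85%).
- Type I error: 1 − 0.8515 − 16 × 0.01 × 0.99^28 = 1 − 0.8515 − 0.1208 = 0.0278 (stated 2.8%).
- Power at 15%: 1 − 0.85^16 − 16 × 0.15 × 0.85^28 = 1 − 0.0743 − 0.0253 = 0.9004 (stated 90.04%).

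All three agree, so the design has been read correctly.

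**Step 2. Intervals.** Blaker's interval holds every rate p whose acceptability is at least 0.05. The acceptability is the smaller tail probability at the observed count plus the largest opposite-tail probability that does not exceed it.

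| Responders | Blaker 95% CI | Clopper-Pearson lower bound |
|---|---|---|
| 2/29 | 1.2% to 21.6% | 0.85% |
| 6/29 | 9.4% to 39.3% | 8.0% |
| 7/29 | 11.0% to 42.9% | 10.3% |
| 8/29 | 13.6% to 46.5% | 12.7% |
| 9/29 | 16.4% to 50.0% | 15.3% |
| 6/30 | 9.1% to 38.0% | 7.7% |
| 8/30 | 13.1% to 44.9% | 12.3% |
| 9/30 | 15.8% to 48.3% | 14.7% |

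The row for 2 or more holds under Blaker (lower bound 1.2%, above 1%) but not under Clopper-Pearson (0.85%). So the table matches the named method there and departs from it at 6.

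**Step 3. Direct check at 15%, n = 29.**
- P(X ≥ 6) = 1 − (0.0090 + 0.0459 + 0.1135 + 0.1803 + 0.2068 + 0.1825) = 0.262. This already exceeds 0.05, so 15% lies inside the interval for 6/29.
- P(X ≥ 8) = 0.059, still above 0.05, so 15% is inside for 8/29.
- P(X ≥ 9) = 0.0223. The largest lower tail not above this is P(X = 0) = 0.0090. The sum is 0.0313, below 0.05, so 15% is excluded at 9/29.

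**Step 4. Other methods at 6/29.** Lower bounds: Wilson 9.9%, Jeffreys 9.1%, Agresti-Coull 9.5%, Wald 6.0%, one-sided 95% Clopper-Pearson 9.4%, one-sided 90% Clopper-Pearson 11.3%. None reaches 15%. The point estimate does not explain the cut-off either, since 5/29 = 17.2% already exceeds 15%.

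**Step 5. How often the claim would be made at a true rate of exactly 15%.** Two-stage probability, removing paths with 0/16:

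| | n = 29 | n = 30 |
|---|---|---|
| 6 or more | 26% | 29% |
| 9 or more | 2.2% | 2.8% |

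At a true 10%, the chance of 6 or more is 6.4% (n = 29) or 7.3% (n = 30).

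**Step 6. Other rows (Blaker).**
- 1/16: 0.3% to 30.0%, contains 1%. 2/16: 2.3% to 36.8%, does not. The stage 1 entry is right only for exactly one responder.
- 0/16: 0 to 20.1%. 1/29: 0.2% to 16.6%. The lower-bound entries in these rows are correct, but both intervals include 15%, so neither supports a conclusion that the rate is at most 1%.

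**The case against.** The strongest reply concerns consequence, not arithmetic. The rule that carries the stated error rates is 0/16 and fewer than 2/29; the tier at 6 appears only in the table, and no enrolment, stopping or power statement depends on it. The protocol requires the exact interval to be reported, so a reader would see roughly 9% to 39% beside any claim. Section 20 describes the data as preliminary and not intended for submission to FDA. The negative rows are worded as matters to consider, and the stage 1 entry changes no action.

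Much of this is fair and limits the reach of the point. The negative rows and the stage 1 entry are errors of statement rather than of decision. It is also true that Blaker's interval is not equal-tailed, so a lower bound at 15% does not guarantee an upper-tail error of exactly 2.5%; the 2.8% for 9/30 shows this.

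None of it rescues the top row. The row issues a prespecified verdict on a primary outcome from a criterion that the count does not meet. Reporting the interval beside the claim would expose the contradiction without resolving it, and the choice between count and interval would then be made after seeing the data.

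**Conclusion.** The concern holds. The entry that 6 or more responders give a lower 95% bound of at least 15% is wrong under the protocol's own method and under every common alternative tried. The true bound at 6 is about 9%, and three counts (6, 7 and 8) would be misdeclared. At a true rate on the 15% boundary the claim would be made in 26% to 29% of trials, against 2% to 3% with a cut-off that meets the stated criterion. The damage is confined to the strongest efficacy claim; the type I error, power and early-termination figures stand.

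This rests on a two-sided 95% Blaker interval with 29 or 30 evaluable subjects. The intervals treat the final count as a single binomial sample, ignoring the stage 1 look. That hardly matters here: at 15% and n = 29 the look changes P(X ≥ 6) only from 0.2621 to 0.2615.

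**What to change.** Before any response data are reviewed, take one of two routes for the top tier:

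- Change the count from 6 to 9, and limit the row above it to 2 to 8 responders so that the rows no longer overlap. This is valid for Blaker at both 29 and 30 subjects. Name Blaker in the table, because Clopper-Pearson at 9/30 gives 14.7% and would need 10.
- Or delete the tier and report the interval. Keeping a row at 6 with a corrected conclusion is possible, but it would only repeat the row for 2 or more.

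Also state in the stage 1 row that the interval contains 1% only at exactly 1/16. Replace the two conclusions that the rate is at most 1% with a statement that 1% is not excluded and that rates up to about 20% (0/16) or 17% (1/29) remain compatible. Reconcile the 14 additional subjects in the table with the total of 29 in the text.

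The cost is a table edit, with no change to sample size, the interim rule or the stated error rates. With the cut-off at 9 the strongest claim becomes harder to reach: at a true rate of 30% and 29 subjects, the chance of 9 or more is 52%.
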